### Implementation

Feedback on the Rebee device and application will be collected from the intervention group through 6 close-ended questions and 1 open-ended question at the end of the study (Multimedia Appendix 1). Specifically, feedback will be collected on the ease of use of the Rebee app and exercises, the ability to complete Rebee exercises independently, any technical issues encountered, the overall user experience, the suggested improvements, and whether they would recommend this technology to others. A simple descriptive analysis will be conducted to summarize the quantitative findings using frequencies and percentages. A content analysis will be performed on the qualitative responses to identify keywords and phrases. If there is substantial variation, we will conduct a thematic analysis to summarize the common themes.

### Adherence Monitoring

Rebee use data for each participant will be retrieved and analyzed via the Rebee software [25]. Use data will be broken down in detail to evaluate daily compliance rate to use of Rebee and its exercises, as well as overall use and uptake over the 12-week period.

### Data Management and Monitoring

#### Overview

All hard copy data will be stored in locked storage spaces at the respective recruitment sites during the study. At the end of the study, all hard copy data will be stored together at one of the recruitment sites. Only authorized study personnel will be able to access these locked cabinets. Survey data will be entered into a password-protected Excel worksheet. We will retrieve data from the electronic medical records upon participant consent. All softcopy data will be password-protected and only accessible to the study team. There is no identifiable data collected on the Rebee application, and only the Rebee team will have access to the nonsensitive data (eg, frequency and duration of rehabilitation exercises).

At the end of the study, all data stored in the Rebee application will be deleted. All softcopy and hard copy data will be maintained for 7 years after study termination and then disposed of in accordance with policy.

Given the minimal risk presented in the use of the wearable device, this study does not involve a data monitoring committee. However, the study team will continuously monitor participant safety through regular reviews of any reported adverse events (AEs), and if any safety concerns arise, the team will report them to the ethics board promptly following the required institutional procedures. There is no interim analysis planned for this study.

#### Trial Monitoring

Safety monitoring will involve monthly checks for any AEs and serious AEs at scheduled time points and whenever needed. The study team will carry out periodic data quality reviews and conduct random monitoring visits to ensure the study is being followed correctly and that data collected is accurate and complete.

## Results

Recruitment took place from January 6, 2025, to September 23, 2025. A total of 407 participants were recruited from January to September 2025, with data collection completed in December 2025. Figure 5 shows the participant progression during the conduct of our study. Data analysis is currently underway, and the first results are expected to be submitted for publication in Q4 2026.

**Figure 5 figure5:**
[figure not shown]
Data collection and analysis workflow.

## Discussion

### Anticipated Findings and Comparison to Prior Work

To the best of our knowledge, this study is the first to determine the clinical effectiveness and cost-effectiveness of an AI-assisted telerehabilitation device with a structured training program starting from inpatient stay and continued upon discharge via an RCT study design among patients requiring postdischarge rehabilitation care in Singapore. We anticipate that patients receiving the telerehabilitation device and structured training program will demonstrate greater improvement in their functional status, as measured by the MBI, compared to those receiving standard rehabilitation alone. We also expect improvements in joint range, physical performance, and quality of life, with reduction in length of CH stay, lower 30-day readmission rates, and increased cost-effectiveness as compared to usual care alone.

Previous studies have demonstrated that telerehabilitation devices can achieve comparable outcomes compared to conventional rehabilitation services [14,15,22]. However, studies are heterogeneous in terms of the type of intervention and technology used, with varying combinations of in-person or digital personnel required for supervision and execution of the program.

### Strengths and Limitations

This trial will contribute in several ways to existing knowledge and research regarding telerehabilitation devices and rehabilitation programs. First, it will test user acceptability and compliance with telerehabilitation devices and systems to guide the practicability of application of such devices to routine clinical practice. Second, this will evaluate the cost-effectiveness of such systems versus usual care alone to provide an economic evaluation encompassing resource use, patient-reported quality of life, and physical function improvement. Finally, this will also test whether the addition of such a telerehabilitation system as compared to usual care alone will improve outcomes in terms of functional improvement, length of stay in a CH, and 30-day readmission rates.

There are some limitations to this study. First, it was not possible to blind participants as the intervention involves receiving a physical Rebee device as well as physical sessions to teach the participant about the use of the Rebee device. This might change the behavior and response of participants in the intervention group, causing them to provide more positive outcomes. The difficulty in blinding participants may also increase patient dropout in the control arm as they do not perceive any immediate benefits to them being in the study. Second, the total health care costs calculated in the cost-effectiveness analysis may be underestimated due to omission of certain costings such as postdischarge service use costs and unplanned readmission costs. These costs were excluded because the data on postdischarge service use were collected through patient self-report and could not be verified. On the other hand, there is insufficient information on readmission costs. To minimize inaccuracy, it was decided that these costings will be excluded from the cost-effectiveness analysis. Another limitation is the language barrier, as the Rebee application is only available in English and Mandarin. Considering that Singapore is a multiracial country, this may deter participants who can only read Malay or Tamil from participating in this study. Finally, there is also a potential confounder, which is the digital literacy of participants, which was not assessed in this study. To address this issue, the study team will provide support to participants and caregivers, ensuring that they are able to operate Rebee independently.

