### Outcome Measures

The primary outcome is functional status measured over 12 weeks. Functional status will be measured using modified Barthel index (MBI), a 100-point ordinal scale for the assessment of a patient’s functional state. The MBI assesses activities of daily living over 10 domains comprising transfers, ambulation, stair climbing, bathing, dressing, toileting, bowel control, bladder control, personal hygiene, and feeding [29].

Secondary outcomes include physical performance, quality of life, length of stay in CH, 30-day readmission rates, and cost-effectiveness over 12 weeks. Patients who are admitted under RDG total knee replacement will have an additional outcome measure of joint range. The outcome measures as well as the method of measurement are listed in Table 3. Health care cost will be calculated from electronic medical records and supplemented with survey data regarding the number of DRC or home therapy sessions attended, manpower hours to train patients to use Rebee, costs of Rebee software and hardware, and use of outpatient community services (eg, day care center, home nursing, housekeeping, and meals on wheels). The tools to be used in this study to measure the outcomes are validated and implemented in routine clinical care.

**Table 3 table3:** Primary and secondary outcome measures.

Variables			Data source, method of measurement, and definitions		Time points
Primary outcome					
	Functional status	Survey: MBI^a^. To establish the degree of independence from any help. A score from 0- 100 using the MBI questionnaire, with 100 being fully ambulant without any help.		Baseline and 4, 8, and 12 weeks	
Secondary outcomes					
	Joint range	Measurement using goniometer on affected knee. Active and passive range of motion (flexion and extension) of affected knee.		Baseline and 4, 8, and 12 weeks	
	Physical performance	Measured by performing 5CST^b^. Measures the time taken to complete 5 sit to stands (in seconds)		Baseline and 4, 8, and 12 weeks	
	Quality of Life	Survey: EQ-5D-5L		Baseline and 4, 8, and 12 weeks	
	Length of stay	Electronic medical records		Date of discharge from CH^c^ minus date of randomization	
	30-day readmission rates	Electronic medical records		12 weeks	
	Direct health care cost	Electronic medical records: cost of inpatient stay		12 weeks	
	Direct health care cost	CRC’s^d^ daily expenditure of manpower		4, 8, and 12 weeks	
	Direct health care cost	Rebee costs: software and hardware		12 weeks	

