The preferred method of imputation will be applied accordingly based on the degree of missingness, such as last observation carried forward.

The cost-effective analysis will evaluate both direct cost savings and cost-effectiveness in terms of quality-adjusted life years (QALYs). To assess direct cost savings, the analysis will evaluate the difference in length of stay at the hospital between the intervention and control group (Table 4). The results will be expressed as mean cost differences between groups. Cost per QALY gained will be evaluated for the cost-effectiveness of the intervention. QALY will be derived using EQ-5D-5L utility scores, and incremental cost-effectiveness ratios (ICERs) will be calculated. The ICERs will be compared to established willingness-to-pay thresholds to determine the cost-effectiveness of the intervention. Sensitivity analyses will be performed to account for uncertainties in cost and QALY estimates. Results will be presented using cost-effectiveness planes and acceptability curve.

**Table 4 table4:** Cost-accounting for the cost-effectiveness analysisa.

Cost category	Cost type	Cost item	Unit of measurement	Source of unit cost	Applicable to
Hardware	Direct	Rebee kits	Per kit per day	Research collaboration agreement	Intervention
Software	Direct	Rebee subscription	Per patient per day	Research collaboration agreement	Intervention
Inpatient care	Direct	Average length of stay	Per patient per day	Electronic medical records	Control and intervention
Manpower	Direct	CRC’s^b^ daily EOM^c^	Per day	Human resource	Intervention

^a^The statistical analysis will be conducted using R (R Foundation for Statistical Computing). All evaluations will be made using 2-side *P* values at the 5% level of significance.

^b^CRC: clinical research coordinator.

^c^EOM: expenditure of manpower.

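### The article gives two different cost sets for the 12-week cost-effectiveness analysis, and the narrower one leaves post-discharge care uncosted apart from the programme itself

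*Protocol article*

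**What the plan says.** The Outcome Measures section of the protocol article lists among the secondary outcomes "length of stay in CH, 30-day readmission rates, and cost-effectiveness over 12 weeks". Its text says that health care cost will come from electronic medical records, "supplemented with survey data regarding the number of DRC or home therapy sessions attended", along with Rebee training hours, Rebee costs and outpatient community services such as day care and home nursing.

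Table 3, in the same section, shows only three direct cost lines: inpatient stay, the coordinator's daily manpower expenditure, and Rebee software and hardware. Table 4, under Statistical Analyses, has the same content. Inpatient care applies to both arms; kits, subscription and manpower apply to the intervention arm only.

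On direct savings, Statistical Analyses states: "To assess direct cost savings, the analysis will evaluate the difference in length of stay at the hospital between the intervention and control group". It then derives QALYs from EQ-5D-5L utilities, forms ICERs and compares them with willingness-to-pay thresholds.

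Strengths and Limitations acknowledges the "omission of certain costings such as postdischarge service use costs and unplanned readmission costs". For service use the reason is that "the data on postdischarge service use were collected through patient self-report and could not be verified"; for readmissions, that too little is known about their cost. It concludes: "To minimize inaccuracy, it was decided that these costings will be excluded from the cost-effectiveness analysis". The consequence it names is that total health care cost might be too low.

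**The concern.** There are two linked problems. First, the article makes two incompatible statements about whether post-discharge therapy and community services enter the cost. A reader cannot tell from Outcome Measures which ICER will be reported.

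Second, the narrower set does not match the time span of the effect measure. The ICER depends on the difference in cost between arms, not on total cost. An omission that lowers both arms equally is harmless; one that differs by arm goes straight into the numerator. The trial hypothesises fewer 30-day readmissions under ATLAS, and the abstract presents such systems as a bridge while patients wait for a DRC place. Differences by arm in the omitted items are therefore plausible on the trial's own reasoning.

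Cost-effectiveness is part of the stated objective, and Future Directions offers the result to policymakers. QALY gains over 12 weeks are small numbers, so modest cost differences move the ratio a long way.

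**Working it through.** **1. The cost items side by side.** Post-discharge service use in Strengths and Limitations is read as the survey-reported therapy and community services of Outcome Measures.

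| Item | Outcome Measures text | Table 3 | Table 4 | Strengths and Limitations |
|---|---|---|---|---|
| CH inpatient stay | Electronic records, not itemised | Yes | Yes, both arms | Not excluded |
| Rebee hardware and software | Yes | Yes | Yes, intervention only | Not excluded |
| Coordinator or training time | Training hours | Daily expenditure | Daily expenditure, intervention only | Not excluded |
| DRC or home therapy | Yes | No | No | Excluded |
| Community services | Yes | No | No | Excluded |
| Unplanned readmission | Not named as a cost | Rate only | No | Excluded |

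The contradiction concerns therapy sessions and community services: one sentence includes them and three other places do not. Readmission cost is a disclosed exclusion and is not contradicted anywhere.

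**2. Time span.** Inputs: EQ-5D-5L at baseline and weeks 4, 8 and 12 (Table 3); usual CH stay of about 3 to 4 weeks (Usual Care). Taking admission as time zero:

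- 3-week stay: (12 − 3)/12 = 75% of the QALY window falls after discharge.
- 4-week stay: (12 − 4)/12 = 67%.

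If enrolment comes some days into a stay of that length, the share is larger. After CH discharge, any cost still accruing under Table 4 belongs to the intervention arm only. The control arm accrues none by construction.

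**3. Effect on the ICER.** Let ΔC be the incremental cost from the Table 4 items, ΔO the omitted cost in the intervention arm minus that in the control arm, and ΔQ the incremental QALYs.

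- Reported ICER = ΔC/ΔQ
- ICER with full costs = (ΔC + ΔO)/ΔQ
- Difference = ΔO/ΔQ, which is zero only if ΔO = 0.

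With ΔQ positive and less omitted care under ATLAS (ΔO negative), the reported ICER is too unfavourable to ATLAS. With more omitted care (ΔO positive), it is too favourable.

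**4. Scale.** The article gives no cost, utility or ICER figure, so there is nothing to reproduce, and every value here is an assumption. A constant utility gain over 12 weeks gives:

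- 0.02 × 12/52 = 0.0046 QALY
- 0.05 × 12/52 = 0.0115 QALY

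Each S$100 of ΔO then moves the ICER by 100 × 52/(0.02 × 12) = S$21,667 or 100 × 52/(0.05 × 12) = S$8,667 per QALY. Over a wider grid:

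| ΔQ | Size of ΔO: S$200 | Size of ΔO: S$500 |
|---|---|---|
| 0.005 | S$40,000 | S$100,000 |
| 0.01 | S$20,000 | S$50,000 |
| 0.02 | S$10,000 | S$25,000 |

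The shift takes the sign of ΔO.

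**The case against.** The case for leaving the plan alone has substance. Table 3, Table 4 and Strengths and Limitations agree with one another, so one sentence is out of line rather than the whole plan. The exclusion is disclosed with reasons. Both arms receive usual care, including post-discharge referral, so different service use is possible but not established. Length of stay, a main hypothesised saving, is costed in both arms. Sensitivity analyses for cost and QALY uncertainty are planned. Cost-effectiveness is secondary to the modified Barthel index. All of this stands and limits the point. It does not resolve the conflicting sentence or the mismatch in time span, and the planned sensitivity analyses are not said to bring back the excluded items.

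Several stronger readings are tempting but unsupported:

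- **The ICER is biased as a matter of fact, or its conclusion would reverse.** Bias requires a difference by arm in the omitted costs, and the magnitudes are all assumed.
- **A transfer to acute care counts as a saving.** Table 3 defines stay as CH discharge minus randomization but does not say how transfers or returns are handled.
- **Research work is charged to ATLAS.** Table 4 applies a daily coordinator cost to the intervention arm, and Randomization and Blinding gives the research coordinator consent and allocation tasks. Nothing says that those tasks are in the daily figure, and a daily rate can be combined with training hours.
- **Self-reported use and assumed readmission costs must be the base case.** The team declined this for stated reasons, and the choice is a trade-off.

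**Conclusion.** The point holds in a limited form. Outcome Measures contradicts Table 3, Table 4 and Strengths and Limitations on post-discharge therapy and community services. The narrower cost set, which also leaves out readmissions, is set against QALYs of which roughly 67% to 75% of the window falls after discharge, given the article's usual stay and admission as time zero.

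Whether the ICER is biased depends on the omitted costs differing by arm. The trial's readmission hypothesis implies that they would, but the direction of the net bias cannot be determined from the documents. The shift of S$10,000 to S$100,000 per QALY illustrates sensitivity; it does not estimate the error. Describing the consequence only as an underestimated total misses the quantity that matters, the between-arm cost difference. The primary analysis of functional status is unaffected.

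**What to change.** 1. Reconcile Outcome Measures, Table 3, Table 4 and Strengths and Limitations so that one cost set is stated.
2. The Table 4 set may remain the base case. If so, label its result as a CH-stay and programme-cost analysis, not as a full 12-week cost per QALY.
3. Add a sensitivity analysis that values the collected self-reported service use at unit costs and the recorded readmissions at a range of assumed unit costs. Specify it before costs are compared by arm; if that comparison has already been made, report the analysis as post hoc.
4. Restate the limitation as possible bias, of unknown direction, in the between-arm cost difference and hence in the ICER.
5. State that coordinator manpower covers only Rebee training and support time, not research tasks.

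The cost is a text correction, a unit-cost look-up and some extra analysis. The service-use data have been collected, and readmissions are taken from electronic records. Table 3 lists readmission rates and not bed-days, so a cost per episode may be the workable unit. The downside is recall error in self-report and reliance on assumed unit costs. Reporting results across the range shows how much either matters.

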### Dissemination Plan

Results from our study will be disseminated through peer-reviewed journals, including publications on the trial protocol, main outcomes, and secondary analyses. Results will also be presented at local and international conferences centered on rehabilitation, DH, and implementation science. Relevant findings will be provided to participating clinical sites and collaborating institutions to inform decisions regarding future adoption and scalability of such telerehabilitation technologies. Dissemination will adhere to ethical, regulatory, and data-sharing requirements.

### Future Directions

Populations around the world are rapidly aging, and health systems are attempting to bend the cost curve by shifting care from hospital-based acute care to community-based preventive health and rehabilitation. The insights on clinical and cost-effectiveness from this study shall also assist policymakers to make better decisions regarding the use of AI-assisted telerehabilitation systems to plug the present gaps in this care transition.

By incorporating both objective clinical measurements as well as health use and cost-effectiveness analyses, this trial aims to extend prior work and provide more evidence and guidance for future scaling of such telerehabilitation models.

## Data Availability

The datasets generated during and/or analyzed during this study will be available from the corresponding author upon reasonable request.

## Appendix

Multimedia Appendix 1 Feedback survey.

Multimedia Appendix 2 SPIRIT 2025 checklist.

## Abbreviations

5CST: 5-time chair stand test
AE: adverse event
CH: community hospital
DH: digital health
DRC: day rehabilitation center
ICER: incremental cost-effectiveness ratio
MBI: modified Barthel index
PRECIS-2: Pragmatic Explanatory Continuum Indicator Summary Framework-2
QALY: quality-adjusted life year
RCT: randomized controlled trial
WHO: World Health Organization
